### Sample size calculation

Using a logistic regression model to predict a 75% partial and completed diabetes remission rate from multiple predictors, a sample size of 150 provides 90% power at the two-sided 5% significance level to detect an OR of 2.0 per SD of any continuous predictor.^52^ This allows for up to 10% of the variation in any one predictor to be explained by the others in the model, and 15% loss to follow-up. The area under the receiver operating characteristic (ROC) curve, overall performance measure, will be estimated with a 95% CI width of at most±0.1 for an area above 0.65. With data analysed from 100 patients there would still be in excess of 80% power to detect the OR of 2.0, and a precision of at most±0.12 for the ROC curve area. This is reasonable enough to allow some deviation in assumptions, such as the dropout rate.

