Initially, the effect of each of the clinical predictors and other covariates (patient demographic factors) of interest on each outcome is to be fitted in univariable models. Any clinical predictor that is significant at a threshold of p value≤0.20 will then be included in a multivariable model predicting the outcome of diabetes remission. Clinical predictors and other covariates will then be eliminated in a stepwise fashion until each remaining predictor is significant at the p value=0.05 threshold and the models are found to be stable. Pattern of fat storage will be measured by visceral adipose tissue (VAT) mass, SAT mass and VAT/SAT ratio, and genes influencing diabetes risk and fat deposition will be measured by the Genetic Risk Score using the approach of Fava *et al*.^51^ These will be added to the model, if not already included, to allow their association with diabetes remission to be formally quantified and tested. We will cautiously extend the model to address other factors in a univariate manner. Internal validation of the selection of the predictive model will be done using bootstrap sampling with re-application of the model selection procedure using at least 1000 replications. The performance of the prediction model under different scenarios will be assessed, primarily by obtaining fitted probabilities of remission from the model to estimate the area under the ROC curve, and also by demonstrating the sensitivity, specificity, positive predictive value and negative predictive value across a series of cut points representing a range of scenarios including high sensitivity, high specificity and equivalent sensitivity and specificity.

Survival curves will be plotted to show the proportion remaining free from diabetes over the longer-term according to categories of predictors identified to be important.

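### The AUC and classification measures are taken from fitted probabilities on the development patients, and the planned bootstrap is not linked to them, so as written they are apparent performance

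*Protocol article*

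**What the plan says.** In the Predictors section of the protocol article, two adjacent sentences have different tasks.

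- **Bootstrap:** "Internal validation of the selection of the predictive model will be done using bootstrap sampling with re-application of the model selection procedure", with at least 1000 replications.
- **Performance:** assessed "primarily by obtaining fitted probabilities of remission from the model to estimate the area under the ROC curve". Sensitivity, specificity, PPV and NPV are then shown at cut points that favour sensitivity, favour specificity or balance the two.

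The earlier paragraph that justifies logistic regression takes the same route: individual predicted probabilities feed the ROC analysis, which gives sensitivity and specificity.

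Sample size calculation names the AUC as the overall performance measure. It says the AUC "will be estimated with a 95% CI width of at most±0.1 for an area above 0.65" and, with 100 patients analysed, claims "in excess of 80% power to detect the OR of 2.0, and a precision of at most±0.12 for the ROC curve area". The primary objective is to develop the model and validate it internally.

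**The concern.** Probabilities fitted by the final model, evaluated in the patients who were used to choose and fit it, give apparent performance. Apparent AUC, sensitivity, specificity, PPV and NPV are optimistic, and more so when many candidates are screened against few events. The article states its primary performance method, and that method contains no correction. The bootstrap that could supply one is assigned to a different purpose.

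The abstract says the model should help direct surgery to patients predicted to reach remission. If the published AUC and predictive values are optimistic by about as much as their quoted precision, a weak model could look usable.

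**Working it through.** **Inputs from the article.** N = 150; OR 2.0 per SD; power 90%, two-sided 5%; 75% remission ("to predict a 75% partial and completed diabetes remission rate from multiple predictors"); an allowance for "up to 10% of the variation in any one predictor to be explained by the others in the model, and 15% loss to follow-up"; univariable screen at p≤0.20; stepwise elimination to p = 0.05; VAT, SAT, VAT/SAT and the genetic risk score then added if absent (four terms); 17 rows in Table 3.

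**1. Reproduce the sample size.** n = (z₀.₉₇₅ + z₀.₉₀)² / [p(1−p)(ln OR)²] / (1−R²) = (1.960 + 1.282)² / [0.1875 × 0.4805] / 0.9 = 129.6, so 130 evaluable. 130 × 1.15 = 149.5, which gives 150; dividing by 0.85 gives 153. The figure reproduces. It concerns the power to detect one predictor, not the performance of a selected model.

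**2. Reproduce the AUC precision.** The Hanley–McNeil standard error for a fixed score is SE² = [A(1−A) + (n₁−1)(Q₁−A²) + (n₀−1)(Q₂−A²)] / (n₁n₀), with Q₁ = A/(2−A) and Q₂ = 2A²/(1+A). At A = 0.65, Q₁ = 0.4815, Q₂ = 0.5121 and A² = 0.4225.

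| Analysed | Remitters / non-remitters | 1.96 × SE | Stated |
|---|---|---|---|
| 150 | 112.5 / 37.5 | ±0.096 | ±0.1 |
| 127.5 (150 × 0.85) | 95.6 / 31.9 | ±0.104 | not given |
| 100 | 75 / 25 | ±0.118 | ±0.12 |

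Both stated values match a score fixed in advance; the formula has no term for selection or fitting. After the 15% loss, the half-width falls to ±0.100 at AUC 0.68 and ±0.097 at 0.70, so the excess over ±0.1 is confined to about 0.65 to 0.68.

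**3. Information available.** 127.5 × 0.25 ≈ 32 non-remitters. Against them stand 17 rows of candidates, or roughly 35 parameters if medication classes, personality scales, ectopic fat sites and liver scores are counted singly (an approximate count).

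**4. Size of the optimism.** The procedure was simulated: univariable screen at 0.20, backward elimination to 0.05, four terms added. The AUC in the development data was compared with the AUC of the same fitted model in a 20,000-patient reference population, over 400 trials per setting. Assumptions not in the article: pairwise correlation 0.1; one true effect of OR 2.0 per SD, or three or five with log-odds 0.4 per SD; the added terms carry no effect of their own.

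| Analysed | Candidates | Added terms | Remission | True effects | Apparent AUC | AUC in new patients | Optimism |
|---|---|---|---|---|---|---|---|
| 128 | 20 | 4 | 75% | 1 | 0.740 | 0.624 | 0.116 |
| 128 | 20 | 4 | 75% | 3 | 0.743 | 0.612 | 0.131 |
| 128 | 20 | 4 | 75% | 5 | 0.785 | 0.655 | 0.130 |
| 128 | 30 | 4 | 75% | 1 | 0.755 | 0.617 | 0.138 |
| 128 | 30 | 4 | 75% | 3 | 0.760 | 0.600 | 0.160 |
| 128 | 30 | 4 | 75% | 5 | 0.803 | 0.657 | 0.146 |
| 128 | 20 | 0 | 75% | 1 | 0.721 | 0.634 | 0.087 |
| 128 | 20 | 4 | 40% | 1 | 0.729 | 0.636 | 0.092 |

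A separate simulation at 128 analysed gave 0.09 with 17 candidates and no added terms, 0.11 with 17 candidates and four added, and 0.15 with 30 candidates and four added. At 100 analysed, with 20 or 30 candidates and four added terms, optimism was 0.14 to 0.19.

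**5. Bias or width?** Suppose a fixed-score 95% interval were placed around the uncorrected AUC. At 128 analysed it would cover the model's true AUC in 13% to 38% of trials (48% to 54% in the last two settings of the table). In the first six settings, the SD of apparent minus true AUC was 0.046 to 0.067, against a fixed-score SE of about 0.04 to 0.046. The interval is therefore about 1.1 to 1.5 times too narrow, and most of the lost coverage comes from bias.

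**The case against.** The strongest reply is that the article already plans the right resampling. A bootstrap that repeats the selection is what an optimism correction needs, the performance sentence follows directly, and the primary objective speaks of validating the model. Saying that an AUC is computed from fitted probabilities need not mean that the uncorrected value will be the headline. A full analysis plan, not shown, may make the link. This stands in part: overstatement is not certain. It does not remove the point, because the article does state the primary method and assigns the bootstrap to the selection alone.

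A reader might also infer that the published confidence intervals will be too narrow. The documents do not support that: ±0.1 is a planning figure, and nothing fixes how the final interval is computed. Nor can the absence of calibration or shrinkage be held against an article, since these may sit in the analysis plan. The cut points are a displayed series, with no single optimised threshold promoted, so the issue there is evaluation in the same patients.

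The ±0.104 against ±0.1 is close to rounding, and the article offers a fallback at 100 patients. That part is secondary.

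Finally, the article calls the study preliminary and requires external validation. This limits the harm but does not correct the figures published first.

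**Conclusion.** The point holds conditionally and should be acted on. If performance is reported as the Predictors section words it, the AUC is apparent and would be too high by roughly 0.09 to 0.16 at about 128 analysed patients, comparable to the quoted ±0.1. The direction is secure. The size depends on the number of candidates (17 to 30), their correlation, the number and strength of true effects (1 to 5), and whether the added terms predict anything; the article gives none of these as modelling inputs. Sensitivity, specificity, PPV and NPV share the problem, but their optimism was not quantified here.

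The stronger reading, that performance is bound to be overstated, goes too far: the planned bootstrap could supply the correction once it is tied to these measures. The ±0.1 and ±0.12 figures are correctly computed for a fixed score and need a label, not a new calculation.

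**What to change.** **Predictors section.** State that the 1000 or more replications already planned will repeat every modelling step: screening, stepwise elimination, addition of the fat and genetic terms, any later extension, and the rule that sets each cut point. In each replication, take the AUC of the resampled model in its own bootstrap sample minus its AUC in the original patients. Subtract the mean of these differences from the apparent AUC, and do the same for sensitivity, specificity, PPV and NPV. Report the corrected values, with bootstrap intervals, as the primary performance for both remission outcomes. Show apparent values only alongside.

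**Sample size calculation.** Describe ±0.1 and ±0.12 as fixed-score planning precision that makes no allowance for model building, and note that at AUC 0.65 after the 15% loss the value is about ±0.104.

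**Cost.** Slightly more analysis within a bootstrap already planned, and a lower reported AUC. No extra patients or measurements are needed.

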## Abstract

**Introduction:**

Type 2 diabetes mellitus (T2DM) and obesity are pandemic diseases that lead to a great deal of morbidity and mortality. The most effective treatment for obesity and T2DM is bariatric or metabolic surgery; it can lead to long-term diabetes remission with 4 in 10 of those undergoing surgery having normal blood glucose on no medication 1 year postoperatively. However, surgery carries risks and, additionally, due to resource limitations, there is a restricted number of patients who can access this treatment. Moreover, not all those who undertake surgery respond equally well metabolically. The objective of the current research is to prospectively investigate predictors of T2DM response following metabolic surgery, including those directly involved in its aetiopathogenesis such as fat distribution and genetic variants. This will inform development of a clinically applicable model to help prioritise this therapy to those predicted to have remission.

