DPP-IV, Dipeptidyl peptidase-IV; FIB-4, Fibrosis-4 score; GLP-1, Glucagon-like peptide 1; HOMA, Homeostatic model assessment; MRI, magnetic resonance imaging; NAFLD, Non-alcoholic fatty liver disease; SGLT-2, sodium-glucose co-transporter-2; TCI-R, Temperament and Character Inventory-Revised.

A logistic regression model predicting diabetes remission assessed at the 15 months visit will be built using the prospective cohort data. This was chosen in preference to an ordinal regression approach, such as the proportional odds model, because of the need to have a clear and independent interpretation of the predictive contribution both to complete remission and to complete and partial remission. Logistic regression was preferred over another alternative approach, discriminant analysis, for the same reason and because logistic regression provides predicted probabilities for individual patients which can then be used within ROC curve analysis to provide estimates of sensitivity and specificity of the regression models measuring their accuracy to predict the diabetes remission outcome of metabolic surgery.

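### The stated performance measures cover discrimination and classification only; none compares predicted with observed remission, and this selection procedure is likely to give probabilities that are too extreme

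*Protocol article*

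**What the plan says.** The Predictors section fixes how performance is judged. The main measure is obtained "primarily by obtaining fitted probabilities of remission from the model to estimate the area under the ROC curve". The others are "sensitivity, specificity, positive predictive value and negative predictive value across a series of cut points", the cut points standing for "a range of scenarios including high sensitivity, high specificity and equivalent sensitivity and specificity". The Sample size calculation repeats the emphasis, "The area under the receiver operating characteristic (ROC) curve, overall performance measure", and gives precision for that measure alone. Validation is internal: "Internal validation of the selection of the predictive model will be done using bootstrap sampling with re-application of the model selection procedure", with at least 1000 replications. No section mentions calibration, shrinkage or an overall error score such as the Brier score.

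The stated purpose goes beyond ranking. The primary objective is to develop and internally validate a prediction model, and the Abstract wants a "clinically applicable model to help prioritise this therapy to those predicted to have remission". Individual probabilities also appear as one reason for preferring logistic regression to discriminant analysis: "for the same reason and because logistic regression provides predicted probabilities for individual patients which can then be used within ROC curve analysis".

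**The concern.** AUC uses only the order of the predictions. Sensitivity, specificity and predictive values at a cut point chosen to reach a given sensitivity or specificity also depend only on order. A model can therefore do well on every listed measure while its probabilities are wrong.

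This matters here because data-driven selection among many candidates in a small sample typically gives coefficients that are too large, so low predictions are too low and high ones too high. The error is greatest among patients with low predictions, the group that a prioritisation tool would place last. Any later cohort used for external validation would start from the uncorrected equation.

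**Working it through.** **1. Patients available.** The inputs are in the Sample size calculation: 75% remission, OR 2.0 per SD, two-sided 5%, 90% power, 10% of a predictor's variation explained by the others, 15% loss, N=150.

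- n = (1.960+1.282)² / [0.75×0.25×(ln 2)²] = 10.51/0.0901 = 116.6
- ÷0.90 = 129.6; ÷0.85 = 152.5. Alternatively 130×1.15 = 149.5, the stated 150.
- Analysed: 150×0.85 = 127.5. Non-remitters: 0.25×127.5 = 31.9.
- AUC half-width at 0.65 (Hanley–McNeil): 0.096 at 150, 0.104 at 127.5 and 0.118 at 100, in line with the stated ±0.1 and ±0.12.

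The plan's figures are reproduced closely and are not in dispute.

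**2. What the listed measures can register.** Let g be any strictly increasing function. Then g(p₁)>g(p₂) exactly when p₁>p₂, so AUC is unchanged. A cut point c set to reach 90% sensitivity becomes g(c) and classifies the same patients.

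A simulated population of 200,000 illustrates this (75% remission; assumed two independent predictors with OR 2.0 per SD):

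| Predictions | AUC | Sens/spec/PPV/NPV at 90% sensitivity | Mean predicted (observed 0.749) | Lowest decile, predicted (observed 0.406) | Brier |
|---|---|---|---|---|---|
| Calibrated | 0.7385 | 0.900/0.348/0.805/0.538 | 0.750 | 0.403 | 0.161 |
| Too extreme (slope 0.5) | 0.7385 | 0.900/0.348/0.805/0.538 | 0.692 | 0.127 | 0.179 |
| Shifted by −1 logit | 0.7385 | 0.900/0.348/0.805/0.538 | 0.563 | 0.203 | 0.199 |

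The rows also agree at 90% specificity and at equal sensitivity and specificity. Only comparisons of predicted with observed risk separate them.

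**3. Is miscalibration likely under this plan?** The p≤0.20 screen and elimination to p=0.05 were simulated and the models applied to new patients. Table 3 has 17 rows, several holding more than one variable, and is offered as examples. The candidate counts, their independence and the effect sizes are therefore assumptions. The later addition of fat-distribution and genetic terms is not included.

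| n | Candidates | True predictors | Median calibration slope | Given ≤40%: mean predicted | Given ≤40%: observed |
|---|---|---|---|---|---|
| 127 | 17 | 5 at OR 1.5 | 0.46 | 28% | 54% |
| 127 | 17 | 2 at OR 2.0 | 0.69 | 28% | 45% |
| 127 | 36 | 5 at OR 1.5 | 0.32 | 25% | 59% |
| 127 | 36 | 2 at OR 2.0 | 0.49 | 26% | 51% |

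Other settings agree. With two true predictors at OR 2.0, the slope is 0.63 (n=127, 20 candidates), 0.52 (n=127, 30) and 0.54 (n=100, 20). With five true at OR 2.0 it is 0.68 (17 candidates) and 0.51 (36), and patients given 40% or less remit in about 38–43%. Across all settings the mean prediction in that group is 22–29%. Where counted, the group was 7–9% of patients.

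**4. Does the remedy help?** Multiplying the linear predictor by the mean bootstrap slope lowered the root mean square error of the predicted probabilities, for example from 0.162 to 0.135 and from 0.151 to 0.137. In a smaller run (50 samples, 40 replicates each) the bootstrap put the slope at 0.59 and 0.44 against true values of 0.52 and 0.39. Shrinkage brought it to about 0.9.

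**The case against.** The strongest reply has four parts.

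- **Overfitting would not go unnoticed.** A bootstrap that repeats selection can expose the gap between apparent and true AUC, for example 0.774 against 0.693 (n=127, 20 candidates). If cut points from the development data are carried forward, the classification measures move too. With five true predictors at OR 2.0 among 17 or 36 candidates, sensitivity set at 90% fell to 86% or 85% in new patients, and specificity set at 90% fell to 80% or 75%. This stands, so a claim that validation is blind to overfitting would go too far. These drops still do not show whether a stated 28% means 28% or 54%, and they provide no correction.
- **There is no contradiction over logistic regression.** A reader might infer that individual probabilities are the reason for the method and are then left unchecked. The article's first reason is clear, independent interpretation of predictive contribution. Probabilities come second, only against discriminant analysis, and the same sentence assigns them to ROC analysis. This stands; the argument rests on the Abstract's purpose and the primary objective.
- **The article is condensed and the study preliminary.** An analysis plan not shown may add calibration, and the article defers to external validation. Nothing in it says that patients will be told a probability. This limits the harm that can be claimed. However, the article names its primary and secondary measures, so this is a stated choice and not merely an omitted detail.
- **The sizes depend on assumptions.** They do, which is why a range is given. In every setting tried, the median slope was below 1.

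**Conclusion.** The concern holds in a limited form. As stated, the performance measures assess discrimination and classification, and none compares predicted with observed remission. With about 127 analysed patients, about 32 non-remitters and two-stage selection by p-value, predictions are likely to be too extreme: a slope of roughly 0.3–0.7, and observed remission of about 38–59% where the model says 22–29% on average.

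These figures assume 17–36 independent candidates with 2–5 true effects of OR 1.5–2.0 per SD, and they concern partial plus complete remission. The complete-remission model was not simulated. The slope also varies between samples: its 10th to 90th percentile range was 0.36–1.01 at n=127 with 20 candidates.

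The documents do not support the readings that the article contradicts its own rationale, that its validation would miss overfitting altogether, or that calibration must rank equally with AUC, which is a matter of preference. The change is worth making before analysis. It does not affect the sample size, visits or outcome.

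**What to change.** For each outcome model, in the bootstrap already planned with selection repeated:

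1. Apply each replicate model to the original sample and estimate its calibration slope and intercept.
2. Report these with a calibration plot alongside the optimism-corrected AUC.
3. Present the final equation with the linear predictor multiplied by the mean bootstrap slope and the intercept re-estimated.

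If an analysis plan already provides for this, a sentence in the performance paragraph of the Predictors section is enough.

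The cost is a few lines of code. Reported ORs become smaller and predictions less spread out, and AUC does not change because scaling by a positive constant keeps the order. The bootstrap slope is itself imprecise and in the runs above was somewhat too high, so shrinkage reduces the miscalibration without removing it.

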### Patient and public involvement

Patients were consulted about the study objectives and selected study procedures to assess acceptability.

## Ethics and dissemination

This study complies with the Declaration of Helsinki and the principles of Good Clinical Practice. The researchers plan to disseminate results at conferences, in peer-reviewed journals as well as lay media and to patient organisations.
